#### Length of hospital stay (LOS)

Length of stay is used as a surrogate for recovery after surgery. We measure number of days from surgery (day 0) till discharge and also number of days in hospital within 90 days after surgery.

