## Methods/design

An ongoing multicenter, randomised clinical trial with 1:1 ratio allocation of participants to either: (1) smoking and/or alcohol cessation intervention initiated 1–2 weeks before radical cystectomy and lasting for a total of 6 weeks, or (2) treatment as usual (Fig. 1). The study was initiated in November 2014 and till now 77 patients have been enrolled (Table 1), an average of two to three patients per month. We aim to enrol a total of 110 patients with expected completion of patient accrual in November 2017.

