## Objectives of the STOP-OP trial

### Postoperative morbidity

The primary outcome is the proportion of patients who develop any postoperative complication, or death, within 30 days after surgery. Secondary outcomes are: types and grades of complications within 30 and 90 days after surgery assessed using the Clavien-Dindo classification [27] of surgical complications. Evaluation of postoperative complications is performed prospectively through patient interviews at all follow-up meetings and retrospectively by a urologist unaware of the patients’ group allocation.

Previous studies of intensive preoperative smoking cessation interventions report 65% and 49% reductions in overall postoperative complications [10–12], and preoperative alcohol cessation interventions a 74% reduction [9]. We assume that 50% of the project patients develop one or more complications after radical cystectomy. Our aim is to reject or confirm a reduction in the number of patients who develop any postoperative complication from 50% to 25%. With a type-1 error risk of 5% and a type-2 error risk of 20% (80% power), the required sample size is 55 patients in each group.

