### Statistics

The data are not expected to be normally distributed, so nonparametric tests are performed. Continuous variables are presented as medians and ranges or means and standard deviations (SD) as appropriate. Categorical variables are presented as counts. Their associated 95% confidence intervals (CI) and *p* values will be provided. The effect of the intervention on risk of postoperative complications and smoking/alcohol abstinence is analysed by Fisher’s exact test. Estimates of the difference between treatment groups will be reported as relative risks (RR) with 95% confidence intervals and *p* values. Effects of the intervention on LOS and HRQoL scores are analysed by Mann-Whitney’s *U* test. Analysis adjusting for institution is also performed by logistic regression models. Effects are considered statistically significant if *p* values are less than 0.05.

We will conduct all analyses using intention-to-treat principles. All analyses are done blinded by an independent researcher. We will use R 3.2.2 [28] to perform all analyses.

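### Days in hospital within 90 days ranks an early death as good recovery, and days till discharge has no value for an in-hospital death

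*Protocol article*

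**What the plan says.** All of this is in the Protocol article.

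- **Meaning of the measure** (Length of hospital stay): "Length of stay is used as a surrogate for recovery after surgery". Fewer days are therefore read as better recovery.
- **Definition** (same section): "We measure number of days from surgery (day 0) till discharge and also number of days in hospital within 90 days after surgery".
- **Test** (Statistics): "Effects of the intervention on LOS and HRQoL scores are analysed by" the Mann-Whitney U test.
- **Analysis set** (Statistics): "We will conduct all analyses using intention-to-treat principles".
- **Death elsewhere** (Postoperative morbidity): "The primary outcome is the proportion of patients who develop any postoperative complication, or death, within 30 days after surgery".

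The article does not say how a patient who dies in hospital, or within the 90 days, enters either stay measure.

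**The concern.** A count of hospital days in a fixed window cannot tell a patient who went home from a patient who died: both stop adding days. Where the count is a resource-use figure, that is accurate. Where it stands for recovery and is ranked with few days as good, an early death is placed at the favourable end. The same patient is then a failure in the primary outcome and a near-best value in a secondary recovery outcome.

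The index stay has a different difficulty. A patient who dies in hospital is never discharged, so the stated interval has no end point. If the day of death is used, an early death again looks like a fast recovery. If the patient is left out, the comparison loses patients because of an event after randomisation, which is hard to square with intention to treat.

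At stake is how the stay comparison reads if early deaths differ between arms: a real benefit could be hidden, or an arm with more early deaths could look as if it recovers faster.

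**Working it through.** **The plan's own figure.** The article states: "With a type-1 error risk of 5% and a type-2 error risk of 20% (80% power), the required sample size is 55 patients in each" of the two arms, for complication rates of 50% and 25%. The two-sided formula with unpooled variance gives (1.960 + 0.842)² × (0.50 × 0.50 + 0.25 × 0.75) / 0.25² = 7.849 × 0.4375 / 0.0625 = 54.9, rounded up to 55. The figure reproduces. It is used below only for the arm size, with the 1:1 allocation given under Methods/design.

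**What the definitions do.** Take three illustrative patients:

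| Patient | Days in hospital within 90 days | Days from surgery till discharge | Days alive and out of hospital |
|---|---|---|---|
| Discharged day 9, alive at day 90, no readmission | 9 | 9 | 90 − 9 = 81 |
| Dies in hospital on day 3 | 3 | undefined | 0 |
| Discharged day 9, dies at home on day 20 | 9 | 9 | 20 − 9 = 11 |

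On 90-day hospital days, the death on day 3 beats the survivor and the death on day 20 ties with the survivor. On days alive and out of hospital, both deaths rank below the survivor.

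**Largest effect of one death.** With 55 per arm, SD(U) = √(55 × 55 × 111 / 12) = 167.3. Moving one patient from best to worst rank changes U by at most 55, so z changes by at most 55 / 167.3 = 0.33. Three excess deaths give at most about 3 × 0.33 = 1.0. Against a neutral middle rank, the distortion is at most half: 27.5 / 167.3 = 0.16 per death.

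**Fixed illustration.** Both arms have the same stays (evenly spaced from 5 to 25 days), and some control patients are then made deaths. The figure is the probability that a control stay exceeds an intervention stay; 0.50 means no difference.

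| Extra control deaths | Counted as a 3-day stay | Given the worst rank |
|---|---|---|
| 1 | 0.491 | 0.509 |
| 3 | 0.473 | 0.528 |
| 6 | 0.446 | 0.556 |

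Counting deaths as short stays moves the comparison towards the arm with more deaths, by about 0.01 per death. None of these shifts is significant alone; with six deaths p is 0.33 and 0.32.

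**Simulation with no true difference in stay.** Assumed: 55 per arm, log-normal stay with median 9 days and log-SD 0.5, the intervention arm having the lower mortality, day of death taken as the end of the stay. Positive z means the control arm looks better.

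| Mortality, intervention v control | Day of death | Mean z |
|---|---|---|
| 1% v 3% | 1-6 | about +0.15 |
| 1% v 6% | 1-6 | about +0.4 |
| 1% v 6% | 1-30, in hospital until death | about −0.14 to −0.18 |
| 1% v 6% | 5-30, in hospital until death | about −0.27 |

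With worst rank for deaths, 1% v 6% on days 1-6 gives about −0.46, in favour of the arm with fewer deaths.

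**Simulation with a true effect.** Assumed: the intervention shortens stay by 20%, a quarter of patients are readmitted, and deaths fall on days 1-7.

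| Deaths, control v intervention | Power, counted as short stays | Power, excluded | Power, worst rank |
|---|---|---|---|
| 3 v 1 | 33% | 45% | 54% |
| 5 v 1 | 20% | 45% | 65% |

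With 2 v 2 deaths and no effect on stay, the rejection rate is about 4-5% under each rule, so balanced deaths do little harm.

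**The case against.** The strongest reply has four parts.

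*The article is condensed, and a rule for deaths may stand in a fuller plan.* This holds for the index stay: the lack of a rule there is not in itself an error. It does not dispose of the 90-day measure. There the variable, its meaning as recovery, the rank test and the analysis set are all published, and together they produce the ranking described.

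*The direction rests on when deaths occur.* This stands. A reader might infer that the arm with more deaths always looks better, against the primary outcome. The documents do not support that: the primary outcome counts deaths to day 30, and nothing says they cluster in the first week. A patient who dies after a long stay or several readmissions has a high count and already ranks badly.

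*Nothing says a death is a short index stay.* Also correct. A reader might infer that both measures score death as a quick discharge. For days till discharge the text leaves the value undefined; treating the death as a discharge is only one reading.

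*The outcome is secondary, and deaths are visible elsewhere.* Deaths within 30 days enter the primary outcome, and complication grades are reported at 30 and 90 days. This limits the harm but does not correct the stay comparison.

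**Conclusion.** The point holds for days in hospital within 90 days: as defined and tested, an early death ranks as good recovery. For days till discharge, the value for an in-hospital death is undefined and needs a rule.

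The size is modest: at most 0.33 in z per death recoded from best to worst, and a mean z of about +0.15 to +0.4 under the assumed mortality gaps with all deaths on days 1-6. It shrinks or reverses if deaths come later in hospital, and nearly vanishes if deaths are balanced. The mortality rates, death days and stay distribution are all assumptions, because the article gives none of them. The point concerns a secondary outcome and does not touch the primary analysis. It is still worth correcting, because the present definition lets the meaning of the result depend on how many patients die early and in which arm.

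**What to change.** - **90-day measure:** analyse days alive and out of hospital within 90 days as the recovery outcome, with the same Mann-Whitney test. Hospital days may stay as a descriptive resource-use figure.
- **Index stay:** give in-hospital deaths the worst rank in the rank test, and report the median stay among those discharged alive as descriptive.

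The cost is a short amendment to the outcome definition. Hospital days to day 90 are already measured. The article does not say that the date of death is recorded, so it must be available from follow-up or the medical record. With 77 of 110 patients enrolled at publication, the change should be dated and made before outcomes are seen by arm. The downside is small: the index-stay result becomes a rank comparison that combines death and stay, and can no longer be read as a difference in days.

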### Other outcomes

#### HRQoL

We measure health-related quality of life (HRQoL) outcomes using the generic questionnaire EuroQol-5D (EQ-5D) at baseline and postoperatively at 6 weeks, 3, 6 and 12 months after surgery. In addition, we use the disease-specific European Organisation of Research and Treatment of Cancer Questionnaires EORTC-QLQ-C30 and QLQ-BLM30 for patients with bladder cancer at baseline and postoperatively at 6 and 12 months.

Time to return to work or habitual level of activity is a surrogate for recovery after surgery and will be evaluated within 12 months after surgery.

### Statistics

The data are not expected to be normally distributed, so nonparametric tests are performed. Continuous variables are presented as medians and ranges or means and standard deviations (SD) as appropriate. Categorical variables are presented as counts. Their associated 95% confidence intervals (CI) and *p* values will be provided. The effect of the intervention on risk of postoperative complications and smoking/alcohol abstinence is analysed by Fisher’s exact test. Estimates of the difference between treatment groups will be reported as relative risks (RR) with 95% confidence intervals and *p* values. Effects of the intervention on LOS and HRQoL scores are analysed by Mann-Whitney’s *U* test. Analysis adjusting for institution is also performed by logistic regression models. Effects are considered statistically significant if *p* values are less than 0.05.

We will conduct all analyses using intention-to-treat principles. All analyses are done blinded by an independent researcher. We will use R 3.2.2 [28] to perform all analyses.

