Hypothetically, intensive smoking- and alcohol-cessation intervention initiated at the earliest possible time before surgery, and continued for 5 weeks after surgery, could benefit patients undergoing radical cystectomy. Intervention during this period might to some degree improve pathophysiological mechanisms, such as tissue perfusion and oxygen delivery, ciliary and immune function, surgical stress response, arrhythmias and bleeding time [14–17], all of which are beneficial for postoperative recovery. Findings of physiological studies have shown that most of the smoking-induced changes are reversible to some degree, and that the period needed for a substantial improvement is about 6–8 weeks [18, 19]. To our knowledge, the surgical studies on smoking and alcohol intervention for risk reduction have focussed only on either smoking or alcohol cessation in isolation. Since smoking and alcohol drinking often coexist and alcohol use is associated with increased risk of smoking relapse [20, 21], it would be relevant to intervene on both.

The aim of this randomised study is, therefore, to evaluate the effect of a smoking, alcohol or combined cessation intervention starting shortly before surgery, and lasting 6 weeks, on overall complications after radical cystectomy. Secondary objectives are to examine the effect on types and grades of complications, smoking cessation and alcohol cessation, length of hospital stay, health-related quality of life and return to work or habitual level of activity up to 12 months postoperatively.

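### HRQoL scores are compared by a Mann-Whitney test without covariates although every instrument is measured at baseline: valid, but it gives up precision that costs nothing to recover

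*Protocol article*

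**What the plan says.** The HRQoL section of the protocol article has EQ-5D measured "at baseline and postoperatively at 6 weeks, 3, 6 and 12 months after surgery". The bladder cancer instruments follow a shorter schedule: "EORTC-QLQ-C30 and QLQ-BLM30 for patients with bladder cancer at baseline and postoperatively at 6 and 12 months". Every HRQoL score therefore has a baseline value.

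The Statistics section gives its reason for the choice of test, "The data are not expected to be normally distributed, so nonparametric tests are performed", and then names the test: "Effects of the intervention on LOS and HRQoL scores are analysed by" the Mann-Whitney U test. The only adjustment it mentions concerns centre: "Analysis adjusting for institution is also performed by logistic regression models". Baseline HRQoL is named neither as a covariate nor as part of a change score. The Background section lists HRQoL among the secondary objectives.

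**The concern.** A two-sample Mann-Whitney test takes no covariate. If it is applied to follow-up scores, the part of the between-patient variation that the baseline score could explain stays in the error term. The trial plans only 110 patients, sized on a binary complication outcome, so precision for HRQoL is already limited. Intervals wider than necessary could leave a real HRQoL effect undetected or poorly estimated.

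The stated reason does not force this choice. Non-normality bears on the error distribution and the form of the test, not on whether baseline may be used. Rank-based ANCOVA, proportional-odds models, and linear models with robust or bootstrap intervals all accommodate skewed or bounded scores together with a baseline covariate.

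**Working it through.** **Inputs from the article.** 110 patients, 1:1, so 55 per arm; significance at p < 0.05; Mann-Whitney for HRQoL; baseline values for all three instruments. 

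**Assumed, because the article is silent.** Baseline-to-follow-up correlation r from 0.3 to 0.7; a true effect of 0.5 SD where power is shown; a two-sided test; full follow-up unless stated.

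**The plan's own figure.** The 55 per arm is for complications, 50% against 25%. With unpooled variance, (1.960 + 0.842)² × (0.50×0.50 + 0.25×0.75) / 0.25² = 54.94, rounded up to 55. It reproduces. No sample size, SD or target difference is given for HRQoL.

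**Unadjusted Mann-Whitney.** With relative efficiency 3/π = 0.955 against the t-test for normal scores, the smallest effect detectable with 80% power is 2.802 × √(2 / (55 × 0.955)) = 0.55 SD. Power for 0.5 SD is 72.7%.

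**Baseline-adjusted.** Residual variance is 1 − r² of the unadjusted variance, the equivalent unadjusted size is 55 / (1 − r²) per arm, and the detectable effect is 2.802 × √(2(1 − r²) / 55).

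| r | Variance ratio | Equivalent n per arm | More patients | Detectable effect (SD) | Power for 0.5 SD |
|---|---|---|---|---|---|
| 0.3 | 0.91 | 60 | 10% | 0.51 | 78.5% |
| 0.4 | 0.84 | 65 | 19% | 0.49 | 81.6% |
| 0.5 | 0.75 | 73 | 33% | 0.46 | 85.7% |
| 0.6 | 0.64 | 86 | 56% | 0.43 | 90.6% |
| 0.7 | 0.51 | 108 | 96% | 0.38 | 95.7% |

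Part of the step from 72.7% is not due to baseline. An unadjusted linear comparison of normal scores already has 74.6% power (detectable effect 0.53 SD), so the gain from baseline itself at r = 0.3 is about 4 percentage points (78.5 − 74.6).

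**Does the gain survive non-normality?** Simulation with 55 per arm, 3,000 runs per setting, scores rounded and capped at 100 (mean 70 and SD 20 before capping), at r = 0.3, 0.5 and 0.7:

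- Mann-Whitney on follow-up scores: power 71%, 72%, 71%.
- ANCOVA: 75%, 83%, 94%.
- Rank-based ANCOVA: 74%, 82%, 92%.

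Across the normal and capped settings, type I error was 4.4% to 5.4% for every method, Mann-Whitney included.

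**If change scores were tested.** Their variance ratio is 2(1 − r). Since 1 − r² = (1 − r)(1 + r), and 1 + r is below 2 whenever r is below 1, baseline adjustment always has the smaller variance. Simulated power for Mann-Whitney on changes (normal scores) was 56%, 74% and 91% at r = 0.3, 0.5 and 0.7, against 78%, 86% and 95% for ANCOVA.

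**With losses.** At an assumed 20% loss (44 per arm), Mann-Whitney has 63% power for 0.5 SD; ANCOVA has 69%, 77% and 91% at r = 0.3, 0.5 and 0.7.

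**The case against.** The strongest reply is that nothing here is an error. Randomisation makes the Mann-Whitney test valid, and its 5% error rate already covers chance baseline imbalance. This stands. A reader might infer that the HRQoL comparison is biased, or that a baseline difference would pass for a treatment effect; neither the article nor the simulation supports that.

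A reader might also infer that the plan can give no effect estimate on the questionnaire scale. That does not follow. A Hodges-Lehmann shift with its interval is the usual companion to this test, and a condensed article need not name it. Such a shift would still ignore baseline.

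Thirdly, the scores tested might be changes from baseline, with the derivation left to a fuller document. The text does not say so, and that reading would still be less efficient than adjustment. A separate analysis plan may add detail, but the article itself names the test and its reason, so this is a stated choice rather than a gap.

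Fourthly, the correlation may be low: baseline precedes removal of the bladder and follow-up runs to 12 months. This is fair. At r = 0.3 with capped scores, the simulated advantage is only 3 to 4 percentage points of power, and 1 − r² is a linear-model result that is not exact for bounded scores.

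Finally, HRQoL is secondary, sits under other outcomes in the article, and carries no power claim that this choice would undermine. That limits the weight of the point without removing it.

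**Conclusion.** The point holds as a matter of efficiency. The article fixes an analysis that, as written, leaves a collected baseline unused, and the reason it gives does not require this. For an assumed r of 0.3 to 0.7 and full follow-up, adjustment lowers the smallest detectable effect from 0.55 SD to between 0.51 and 0.38 SD. The size of the gain cannot be taken from the article: it is slight at the low end and substantial from about r = 0.5. Validity is not in question and the primary outcome is unaffected. It is a worthwhile improvement to a secondary analysis, of minor to moderate weight.

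**What to change.** Reword the HRQoL sentence in the Statistics section. At each time point, analyse each score with a model containing treatment and the baseline score: ANCOVA with a robust or bootstrap 95% CI or, if a rank method is preferred, rank-based ANCOVA or proportional odds. Add exposure type (smoking, alcohol or both) and site as main effects, pooling small sites. Do not fit the full stratum cells: five sites by three exposure types gives up to 15 cells for 110 patients, and the article's accrual table shows one site with 1 patient and another with 5. Report the adjusted difference with its 95% CI, state how deaths before each assessment are handled, and keep Mann-Whitney as a sensitivity analysis.

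The cost is a change of wording, slightly more analysis work and some reliance on a model. No new data are needed. At the time of the article 77 of 110 patients were enrolled and the analysis was to be blinded, so the change could be made before unblinding.

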**Fig. 1 Fig1:**
[figure not shown]
Trial profile

**Table 1 Tab1:** Accrual of patients to date at the five participating institutions

Institutions	Accrual, *n*
Rigshospitalet, University Hospital of Copenhagen	45
Herlev, University Hospital of Copenhagen	13
Skejby, University Hospital of Aarhus	13
Aalborg University Hospital	5
Odense University Hospital	1

The protocol for this randomised clinical trial is reported in compliance with the Standard Protocol Items: Recommendations for Interventional Trials (SPIRIT) guidelines [22]. See Additional file 1.

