## Research procedures

In connection with the initial planning of surgery, the patient’s designated urologist and a trial nurse approach eligible patients with information about the study and the invitation to participate. Trial nurses at each site randomise patients using a computer-generated, stratified, block randomisation scheme [23]. The randomisation system is accessible around the clock via tablets. This ensures immediate randomisation of patients accepting participation and adequate allocation concealment. Block sizes vary from 2 to 8. Stratification takes place for trial site and smoking, risky alcohol drinking or both.

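### Habit is a stratification factor at randomisation but enters no stated analysis, and the unstratified Fisher test is conservative; the cost is some precision, not bias

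*Protocol article*

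**What the plan says.** On randomisation, the article's Research procedures section states: "Stratification takes place for trial site and smoking, risky alcohol drinking or both". It adds: "Block sizes vary from 2 to 8".

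On the outcome, the section on postoperative morbidity states: "The primary outcome is the proportion of patients who develop any postoperative complication, or death, within 30 days after surgery". The same section sizes the trial at 55 per group for a fall from 50% to 25%, with 5% type-1 error and 80% power.

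On analysis, the Statistics section states: "The effect of the intervention on risk of postoperative complications and smoking/alcohol abstinence is analysed by Fisher’s exact test". It continues: "Estimates of the difference between treatment groups will be reported as relative risks (RR) with 95% confidence intervals". The only adjusted analysis is one sentence: "Analysis adjusting for institution is also performed by logistic regression models". That sentence does not say which outcomes the model covers, and no other sentence brings habit into an analysis.

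**The concern.** Stratified randomisation forces the arms to be alike on the stratification factors. If those factors predict the outcome, the treatment comparison varies less between hypothetical repeats of the trial than an unstratified test assumes. Such a test then rejects too rarely under the null and gives up some power. The usual remedy is to analyse by the factors used to randomise. This plan does so for site, in an additional model, and does not do so for habit.

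This is more than an article leaving detail to a fuller document. The article names the test, the model and the covariate, and the covariate list holds one of the two design factors. In a trial of 110 patients, which the Discussion expects to be hard to recruit, even a few points of power are worth keeping if they cost nothing.

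**Working it through.** **Inputs from the article.** Event rates 50% and 25%; 55 per group; 5% type-1 error; 80% power; site accrual 45, 13, 13, 5 and 1 (total 77, Table 1); block sizes 2 to 8.

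**Assumed, because the article is silent.** A two-sided test, the shares of the three habit groups, and how far risk differs between habits and between sites.

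**Step 1: the plan's own figure.** Unpooled normal approximation, two-sided:

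n = (1.960 + 0.842)² × (0.50×0.50 + 0.25×0.75) / 0.25² = 54.94, so 55 per group. The stated figure is reproduced.

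**Step 2: the named test, with no strata at all.** Exact enumeration of all binomial outcomes at 55 per arm:

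| Test | Power, 50% v 25% | Size, both 50% | Size, both 37.5% |
|---|---|---|---|
| Fisher | 0.721 | 0.028 | 0.031 |
| Unadjusted chi-square | 0.789 | 0.045 | 0.052 |

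The gap to 80% is 80 − 72.1 = 7.9 points. Leaving Fisher for chi-square recovers 78.9 − 72.1 = 6.8 of them, with no use of the strata. Fisher's test needs about 64 per group to reach 80%.

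**Step 3: what stratifying by habit adds when only habit is prognostic.** 4,000 simulated trials per row, 110 patients, Table 1 site shares, assumed habit mix 65/15/20%. The strong row lets risk run from 40% to 78% across habits. Power:

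| Habit effect | Fisher | Chi-square | CMH, habit | CMH, site × habit, unpooled |
|---|---|---|---|---|
| None | 0.756 | 0.793 | 0.792 | 0.770 |
| Moderate | 0.733 | 0.776 | 0.776 | 0.762 |
| Strong | 0.734 | 0.769 | 0.790 | 0.767 |

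Against chi-square, habit stratification gives −0.1, 0.0 and +2.1 points. Fully crossed, unpooled strata give −2.3, −1.4 and −0.2 points. In simulations of the same design, the size of the habit-stratified test was about 5% (0.048 to 0.053), against 0.028 to 0.035 for Fisher.

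**Step 4: both factors prognostic.** 4,000 trials per row, assumed habit mix 70/10/20%, log-odds shifts up to the value shown on each factor. Cells give size / power:

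| Shift | Fisher | Chi-square | Logistic, site only | Logistic, site + habit | CMH, both |
|---|---|---|---|---|---|
| 0 | 0.034 / 0.75 | 0.047 / 0.79 | 0.053 / 0.79 | 0.054 / 0.79 | 0.051 / 0.77 |
| 0.4 | 0.026 / 0.75 | 0.041 / 0.79 | 0.049 / 0.80 | 0.051 / 0.81 | 0.049 / 0.78 |
| 0.7 | 0.026 / 0.76 | 0.034 / 0.80 | 0.044 / 0.82 | 0.053 / 0.84 | 0.049 / 0.82 |
| 1.0 | 0.017 / 0.77 | 0.023 / 0.81 | 0.036 / 0.84 | 0.052 / 0.88 | 0.049 / 0.86 |

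As the strata become more prognostic, the tests that leave out a factor become more conservative, and those that include both hold about 5%. The gain of the two-factor logistic model over chi-square rises from about 0 to 7 points. The upper end needs strong effects of both factors.

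**Step 5: scale.** At the design rates the relative risk is 0.25/0.50 = 0.50 and the odds ratio is (0.25/0.75)/(0.50/0.50) = 0.33. A logistic model yields the second unless it is converted.

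**The case against.** The best defence is that an unadjusted primary test supported by an adjusted analysis is valid. It is also a reasonable choice with 110 patients spread over 5 × 3 = 15 site-by-habit cells. Unpooled stratification over all the cells is no better than chi-square in Step 3. This stands, and it is why the remedy pools small sites.

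The prognostic value of habit is also undocumented. The Background says that smoking and risky drinking each raise risk, but every participant has at least one of them, and nothing in the article compares smokers, drinkers and those who do both. This stands too, and it limits the size of the point.

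A reader might infer four stronger things that the article does not support:

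- *That the power shortfall comes from ignoring the strata.* Step 2 has no strata and shows nearly all of it.
- *That the balance obtained at randomisation goes unused.* Site is in the additional model, and balance helps an unadjusted comparison as well.
- *That the adjusted result contradicts the promised relative risk.* The article never says it will report an odds ratio. Conversion to a relative risk is not excluded and could be described elsewhere.
- *That the site with one patient ("Odense University Hospital") breaks the adjusted model.* The count is interim, at 77 of 110. Even a single-patient site at the end would leave only its own intercept inestimable. The treatment effect would still be estimated, with that patient contributing nothing.

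None of this explains why one of the two stratification factors is missing from every stated analysis.

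**Conclusion.** The point holds as a mismatch between design and analysis with a modest cost: the habit stratum is in no stated analysis, and the primary test is unstratified. The errors are on the conservative side. Nothing here biases the estimate or inflates type-1 error.

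Fisher's exact power of 72% and size of about 3% follow from the article's own rates and sample size, and they come mainly from the choice of Fisher's test. The further loss from omitting habit is about 0 to 2 points of power, larger only if site and habit both matter strongly. That range rests on assumed habit shares and stratum risks. The change is worth making because it is nearly free, not because the trial is invalid without it.

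**What to change.** Before unblinding, restate the primary analysis as a Cochran-Mantel-Haenszel test with the Mantel-Haenszel relative risk and 95% confidence interval. Stratify it by habit (three levels) and by site, with the smallest sites pooled. An acceptable alternative is a logistic model with treatment, habit and pooled site, converted to a relative risk by marginal standardisation so that it matches the promised scale. Name one of the two as primary, and keep the unstratified Fisher test as a sensitivity analysis.

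The cost is wording in the Statistics section, as both factors are recorded at randomisation. The pooling rule must be written down in advance, without reference to outcomes by arm. Pooling matters: fully crossed, unpooled strata lose about 1 to 2 points of power against chi-square if site is not prognostic. The pooled version was not simulated here, so its exact power is not claimed.
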